## Abstract

**Background:**

Severe acute respiratory syndrome coronavirus 2 (SARS CoV-2), the virus responsible for coronavirus disease 2019 (COVID-19), can lead to hospitalisation, particularly in elderly, immunocompromised, and non-vaccinated or partially vaccinated individuals. Although vaccination provides protection, the duration of this protection wanes over time. Additional doses can restore immunity, but the influence of viral variants, specific sequences, and vaccine-induced immune responses on disease severity remains unclear. Moreover, the efficacy of therapeutic interventions during hospitalisation requires further investigation. The study aims to analyse the clinical course of COVID-19 in hospitalised patients, taking into account SARS-CoV-2 variants, viral sequences, and the impact of different vaccines. The primary outcome is all-cause in-hospital mortality, while secondary outcomes include admission to intensive care unit and length of stay, duration of hospitalisation, and the level of respiratory support required.

**Methods:**

This ongoing multicentre study observes hospitalised adult patients with confirmed SARS-CoV-2 infection, utilising a combination of retrospective and prospective data collection. It aims to gather clinical and laboratory variables from around 35,000 patients, with potential for a larger sample size. Data analysis will involve biostatistical and machine-learning techniques. Selected patients will provide biological material. The study started on October 14, 2021 and is scheduled to end on October 13, 2026.

**Discussion:**

The analysis of a large sample of retrospective and prospective data about the acute phase of SARS CoV-2 infection in hospitalised patients, viral variants and vaccination in several European and non-European countries will help us to better understand risk factors for disease severity and the interplay between SARS CoV-2 variants, immune responses and vaccine efficacy. The main strengths of this study are the large sample size, the long study duration covering different waves of COVID-19 and the collection of biological samples that allows future research.

**Trial registration:**

The trial has been registered on ClinicalTrials.gov. The unique identifier assigned to this trial is NCT05463380.

## Background

Since the onset of the coronavirus disease 2019 (COVID-19) pandemic, novel variants of severe acute respiratory syndrome coronavirus 2 (SARS-CoV-2) have emerged. The World Health Organization (WHO) categorises these variants based on level of concern, including variant of interest (VOI), variant of concern (VOC), and variants under monitoring (VUM) [1]. The VOC known as Omicron (B.1.1.529) was designated by the WHO on November 26, 2021 [2]. In contrast, the European Centre for Disease Prevention and Control (ECDC) removed BA.2, BA.4, and BA.5 variants from their list of concern due to their limited circulation [3].

To better understand the impact of these variants, detailed information is needed regarding their severity, mortality rates, disease progression, and the effectiveness of currently available vaccines and therapeutic interventions. Notably, previous reports have suggested increased disease severity for the B1.1.1.7 (alpha) variant compared to other co-existing and previous variants [4–6].

Recent studies have indicated that the Omicron variant poses lower risks of hospital attendance, admission, and death when compared to the Delta variant [7–9]. While the likelihood of severe disease from Omicron is lower compared to previous variants, the sheer volume of cases associated with it has led to a cumulative increase in hospitalisations related to COVID-19, surpassing those caused by other variants [10]. The diminished likelihood of severe disease associated with Omicron could be a result of partial immunity acquired through previous infection or vaccination. Additionally, findings from animal studies, wherein Omicron infections exhibited lower viral levels in infected tissues, lend further support to the notion that Omicron may inherently induce a less severe infection when compared to alternative variants [11].

The influence of different SARS-CoV-2 variants on COVID-19-specific therapies, such as antivirals and immunomodulators, remains to be thoroughly elucidated. Evidence suggests that widely used monoclonal antibody cocktails exhibit reduced efficacy against the Omicron variant, while antivirals continue to be effective [12–17].

The complexity of the situation is further compounded by multiple factors, including immunity derived from prior infections and COVID-19 vaccination. Although the impact of virus variants is presently focused largely on the spike protein, the potential influence of mutations in other regions of the SARS-CoV-2 genome on clinical outcomes and vaccine response necessitates further investigation. Advanced machine-learning techniques can facilitate the analysis of complex relationships between variables in this context.

Thus, our current understanding of the interplay between SARS-CoV-2 variants, disease severity, vaccine efficacy, treatment effectiveness, and immune responses is insufficient, and requires more research. The European Cohorts of Patients and Schools to Advance Response to Epidemics (EuCARE) project, with its access to diverse data from multiple European and non-European countries, including viral sequences, holds significant value.

## Methods and design

### The EuCARE project

The EuCARE project is a collaborative effort between several cohorts of patients and schools across various geographic regions, including European and non-European countries (www.eucareresearch.eu). The project aims to provide an advanced response to COVID-19 epidemics by consolidating or expanding interactions among different clinical centres and research centres. The project brings together a comprehensive, multidisciplinary team of clinicians, virologists, epidemiologists, statisticians, and experts in artificial intelligence. The project aims to investigate several aspects of the COVID-19 pandemic, including natural and vaccine-induced immunity to different viral variants in healthcare workers, the clinical course and long-term follow-up of hospitalised COVID-19 patients, and the best strategies to control the spread of different viral variants in schools [18]. The study focuses on different groups, including hospitalised patients, patients with post-acute sequelae of SARS-CoV-2 infection (PASC), vaccinated healthcare workers (HCW), and school cohorts.

As part of the EuCARE project, Work Package 3 (WP3) has been designed to investigate the impact of COVID-19 on both hospitalised and outpatient populations. WP3 includes two distinct cohorts: the EuCARE Hospitalised Study, which oversees collecting data from COVID-19 patients during the acute phase of hospitalisation, and the EuCARE POSTCOVID Study, which gathers data from both hospitalised and outpatient COVID-19 patients. The focus of this paper is the EuCARE Hospitalised Study, and we present its protocol here.

### Aims and objectives

The aims of this study are to analyse the clinical course of COVID-19 in hospitalised patients in relation to SARS-CoV-2 viral characteristics and vaccines used and to provide recommendations for optimised clinical management and treatment, taking into consideration the viral characteristics and vaccines employed. Data and biological material from COVID-19 inpatients in a diverse setting of twelve hospitals/clinics across eleven countries and four continents are being collected and will be analysed.

The specific objectives of this study are:To describe the patterns of clinical symptoms, therapeutic interventions, and clinical outcomes in patients hospitalised for SARS CoV-2 infection.To assess the impact of viral variants/sequences on clinical outcomes measured by all-cause in-hospital mortality, non-invasive mechanical ventilation/high-flow nasal oxygen, mechanical ventilation, admission to the intensive care unit (ICU), length of ICU stay, and overall length of hospitalisation.To assess the impact of different vaccines and vaccination schedules on clinical outcomes (vaccine effectiveness for progression/pathogenesis) measured by all-cause in-hospital mortality, non-invasive mechanical ventilation/high-flow nasal oxygen, mechanical ventilation, admission to the ICU, length of ICU stay, and overall length of hospitalisation, with the goal of enhancing our comprehension of vaccine hesitancy.To assess the impact of viral variants/sequences, different vaccines and vaccination schedule on response to treatment interventions and the associated clinical outcomes.To provide biological material to Work Package 2 (WP2) in EuCARE for further studies on viral characteristics and associated immune responses.To provide data to Work Package 5 (WP5) in EuCARE for further studies using machine-learning approaches.

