### Study population

The study population includes adult patients (≥ 18 years) who are hospitalised or who have died in the emergency department and have tested positive for SARS-CoV-2 by polymerase chain reaction (PCR) or by an antigen test within 14 days prior to admission or during hospitalisation. The study aims to include both first and recurrent episodes of COVID-19. All study subjects are required to sign informed consent when required by ethical approval. Patients who do not meet these inclusion criteria will be excluded from the study.

The anticipated sample size for the study is 35,000, which is expected to increase depending on the course of the COVID-19 pandemic. Due to the recruitment strategy of the study, the exact sample size cannot be predetermined as it is dependent on the number of patients admitted to participating centres. This approach will provide a diverse cohort of patients from various geographical regions, with a range of demographic and clinical characteristics, thus establishing a robust foundation for the study's research objectives (Fig. 1).

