### Data analysis

Data analysis for this study is tailored to each specific study objective. All final analyses will be conducted by an assigned study statistician or through common statistical packages disseminated to each study site. Descriptive data of the study cohort will be presented with medians and interquartile ranges for continuous variables and number and percentages for categorical variables. This will be presented in an overall, pooled format, as well as stratified by study sites and study time-period.

The main exposure of interest, SARS-CoV-2 variants, will be studied using both the currently described genotypes of main interest and a subset of whole genome sequencing data. Depending on local and temporal variations in circulating variants and the percentage of hospitalised patients with variant classification performed, the variant might be extrapolated based on the current variant distribution.

The primary outcome, in-hospital mortality, will be studied using Cox proportional hazards models and Fine and Gray models, with the underlying baseline hazard function based on the date of admission or the date of the first positive test if tested positive later during hospitalisation. Patients with community-onset and hospital-onset COVID-19 will be analysed both pooled and separately. Competing risks analyses will be used to examine ICU admission, length of hospitalisation, and length of ICU stay, with in-hospital death as a competing event.

Covariate adjustment will be used to control for potential confounding variables, including age, sex, ethnicity, co-morbidities in accordance with risk factors for severe COVID-19 according to the Centre for Disease Control and Prevention (CDC), SARS-CoV-2 vaccination status, and geographical region. Both complete case analyses and analyses based on multiple imputation by chained equations imputed or inverse probability weighted datasets will be performed to account for missing data.

Given the evolving nature of COVID-19, covariates as well as other variables and definitions may change over the course of the pandemic. The effect of various interventions performed during hospitalisation on the study objectives will be evaluated using causal inference methods, including inverse propensity weighting and doubly robust methods, to account for potential treatment biases and violations of positivity assumptions.

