
The study has some limitations that are common to observational studies. These include the potential for unmeasured confounding and confounding by indication. Additionally, missing data for some participants may introduce bias and reduce the statistical power of the analysis. Another potential source of bias is the use of variant genotyping or whole genome sequencing, which may have been conducted selectively for different individuals or at different time periods and study sites. This variability may introduce bias due to differences in indications for variant characterisations at different time periods and study sites.

Overall, the EuCARE-HOSPITALISED study represents a comprehensive and valuable effort to evaluate the association between different circulating variants and in-hospital mortality in COVID-19 patients. The findings of this study may have important implications for patient care, public health policy, and future research endeavours.

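### Length of ICU stay is treated as an effect of variant and vaccine, but it exists only in patients selected into the ICU after exposure

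*Protocol article*

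**What the plan says.** In the protocol article, under Aims and objectives, description of the clinical course is the first objective. The second objective asks for the impact of viral variants and sequences, measured by a list of outcomes that ends with "admission to the intensive care unit (ICU), length of ICU stay, and overall length of hospitalisation". The third applies the same list to vaccines: "To assess the impact of different vaccines and vaccination schedules on clinical outcomes (vaccine effectiveness for progression/pathogenesis".

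Under Data analysis, the method is "Competing risks analyses will be used to examine ICU admission, length of hospitalisation, and length of ICU stay, with in-hospital death as a competing event". The adjustment is "Covariate adjustment will be used to control for potential confounding variables, including age, sex, ethnicity, co-morbidities", followed by vaccination status and geographical region. Causal methods are assigned to treatments given in hospital: "The effect of various interventions performed during hospitalisation on the study objectives will be evaluated using causal inference methods".

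The cohort, under Study population, is "adult patients (≥ 18 years) who are hospitalised or who have died in the emergency department". The limitations in the Discussion begin with "These include the potential for unmeasured confounding and confounding by indication" and go on to missing data and selective genotyping. Selection into the ICU is not among them.

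**The concern.** Because description has its own objective, length of ICU stay in the second and third objectives is an effect target. A time-to-event analysis of an ICU stay starts at ICU entry and ends at ICU discharge or death, so only patients who enter the ICU contribute. Whether a patient enters depends on severity, which variant and vaccination may change; the plan acknowledges this by listing ICU admission as an outcome of the same exposures. Comparing stays within that subset conditions on a consequence of exposure.

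Nothing stated in the plan repairs this. Treating death as a competing event deals with how a stay ends, not with who starts one. The named covariates include no measure of acute severity, and adjustment helps only as far as the covariates capture the severity that drives both admission and stay.

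The results are meant to support recommendations on management and to inform understanding of vaccine hesitancy. An apparent finding that vaccinated patients stay longer in the ICU, produced only by who is admitted, would be unhelpful there.

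**Working it through.** The article gives no ICU rates or stays, so there is no figure of the plan to reproduce and every input below is an assumption.

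**Inputs (assumed).** Severity S is standard normal in the unexposed. Patients above a threshold z enter the ICU. ICU admission is q = 20% without the exposure and 10% with it. Log ICU days rise by b = 0.2 to 0.5 per SD of severity.

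**Mean severity in the ICU:** E[S | S > z] = φ(z)/q.
- q = 0.20: z = 0.842, φ(z) = 0.2800, mean = 0.2800/0.20 = 1.400 SD.
- q = 0.10: z = 1.282, φ(z) = 0.1755, mean = 0.1755/0.10 = 1.755 SD.

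**Three ways to halve ICU admission.** The apparent ratio of stay is exp(b × change in mean severity). The ratio of ICU days per hospitalised patient is 0.10/0.20 = 0.5 times that.

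| Mechanism | Change in mean ICU severity | Apparent stay ratio, b = 0.2 to 0.5 | ICU days per hospitalised patient |
|---|---|---|---|
| Milder admissions prevented, severity otherwise unchanged | 1.755 − 1.400 = +0.355 | 1.07 to 1.19 | 0.54 to 0.60 (down 46 to 40%) |
| Admissions prevented regardless of severity | 0 | 1.00 | 0.50 (down 50%) |
| Everyone's severity lowered by 1.282 − 0.842 = 0.440 SD | (1.755 − 0.440) − 1.400 = −0.085 | 0.98 to 0.96 | 0.49 to 0.48 (down 51 to 52%) |

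In the first two rows the exposure changes no admitted patient's stay, so any ratio other than 1 is an artefact. In the third row each patient's expected stay does fall, by a factor exp(−0.440b) = 0.92 to 0.80, that is by 8 to 20%. The comparison within the ICU shows only 2 to 4%.

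These are ratios of geometric means. With arithmetic means the first row stays at 1.07 to 1.19 and the third is 0.98 to 0.95.

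**Check with a different structure (also assumed).** Take 70% lower-severity patients (ICU risk 10%, mean stay 6 days) and 30% higher-severity patients (ICU risk 30%, mean stay 14 days).
- Without the exposure, admitted fractions are 0.70 × 0.10 = 0.07 and 0.30 × 0.30 = 0.09. Mean stay is (0.07 × 6 + 0.09 × 14)/0.16 = 10.5 days, and ICU days per hospitalised patient are 1.68.
- Let the exposure multiply ICU risk by 0.3 and 0.7 respectively and leave stays alone. The fractions become 0.021 and 0.063. Mean stay is (0.021 × 6 + 0.063 × 14)/0.084 = 12.0 days (+14%), and ICU days per hospitalised patient are 1.01 (−40%).
- If stays are also truly 10% shorter, mean stay among the admitted is 12.0 × 0.9 = 10.8 days, still +3%.
- With the risk ratios reversed (0.7 and 0.3), mean stay is 8.8 days (−16%).

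**Does the competing event help?** In the same two strata, assume daily discharge rates of 1/6 and 1/20 and death rates of 1/60 and 1/30. With risk ratios 0.3 and 0.7, the cumulative incidence of ICU discharge by day 14, with death competing, falls from 0.60 to 0.52 although no rate within a stratum has changed. The artefact remains.

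**The case against.** The strongest reply is that the article nowhere restricts the analysis to ICU patients. It gives no time origin or risk set for this outcome, and such detail may sit in the full protocol or analysis plan, which is not shown. That is fair, and the restriction is an inference. It follows from the outcome itself, however, since there is no ICU stay to time in someone never admitted. The point rests on the stated objective and the stated method, not on a missing detail.

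A reader might infer that the bias always makes a milder variant or an effective vaccine look worse. The document does not support that. The sign depends on which admissions are prevented, and the calculation gives longer, unchanged and shorter stays. A milder variant may plausibly lower severity across the board, in which case the sign is right and the effect is understated.

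There are also partial safeguards. ICU admission and mortality are reported for the same exposures, so a longer stay could be read beside fewer admissions. Vital signs and laboratory values are collected, and the covariate list is open to change, so adjustment for severity is not excluded. These reduce the problem but do not turn the contrast within the ICU into an effect.

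Finally, the whole cohort is already selected on hospitalisation or death in the emergency department, which vaccine and variant may also influence. That stands, and the fix does not remove it.

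**Conclusion.** The point holds in a limited form. As worded, the second and third objectives seek an effect on length of ICU stay, and the natural reading of the stated analysis compares groups selected after exposure. The result is not interpretable as an effect of variant or vaccine, and the direction of the distortion cannot be known in advance. With ICU admission halved from 20% to 10%, apparent stay ranges from 19% longer to 4% shorter across the three mechanisms in the normal model, while ICU days per hospitalised patient fall by roughly 40 to 52% throughout. These sizes rest wholly on assumed rates and slopes. The conclusion about interpretation needs only that severity drives both admission and stay and is not fully measured. The matter concerns one secondary outcome and leaves the primary mortality analysis untouched, so it is a desirable improvement and not a critical fault.

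**What to change.** For the second and third objectives, define the target as ICU days up to a fixed day (for example day 28) in all hospitalised patients, counting zero for those never admitted. Estimate it from a multistate model with states ward, ICU, discharged and dead, and present it beside mortality, because early death also shortens ICU time. Keep length of stay among ICU patients, with death competing, as a descriptive result and label it so.

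The cost is some added analysis. It needs ICU entry and exit dates, which the outcome implies but the section on variables and data collection does not list, so their availability should be confirmed. The new measure mixes how often patients enter the ICU with how long they stay. Selection on hospitalisation remains, so the results should be stated as applying to progression among hospitalised patients.

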### Study design

Observational multicentre combined retrospective and prospective study (Fig. 1).

**Fig. 1 Fig1:**
[figure not shown]
Study timeline, study population, study centres, and study variables

### Study timeline

The study commenced on 14th October 2021 and is expected to conclude on 13th October 2026 (Fig. 1).

### Study population

The study population includes adult patients (≥ 18 years) who are hospitalised or who have died in the emergency department and have tested positive for SARS-CoV-2 by polymerase chain reaction (PCR) or by an antigen test within 14 days prior to admission or during hospitalisation. The study aims to include both first and recurrent episodes of COVID-19. All study subjects are required to sign informed consent when required by ethical approval. Patients who do not meet these inclusion criteria will be excluded from the study.

The anticipated sample size for the study is 35,000, which is expected to increase depending on the course of the COVID-19 pandemic. Due to the recruitment strategy of the study, the exact sample size cannot be predetermined as it is dependent on the number of patients admitted to participating centres. This approach will provide a diverse cohort of patients from various geographical regions, with a range of demographic and clinical characteristics, thus establishing a robust foundation for the study's research objectives (Fig. 1).

### Variables definition and data collection

The variables in this study have been meticulously defined, considering the study objectives and the availability and structure of data at the participating centres. This process involved iterative harmonisation. Adhering to the principles of the General Data Protection Regulation (GDPR), the principle of data minimisation was adopted to facilitate data collection. The collected data encompass various aspects, including demographics, SARS-CoV-2 virological variables, COVID-19-specific treatments, clinical outcomes, vital signs, laboratory parameters, and co-morbidities. These variables are categorised into mandatory and non-mandatory, with the mandatory ones being crucial for addressing the study objectives. Data collection strictly adheres to the study protocol, the most recent version of the Declaration of Helsinki, the International Council for Harmonisation of Technical Requirements for Pharmaceuticals for Human Use – Good Clinical Practice (ICH-GCP) or ISO EN 14155, the GDPR, as well as all applicable national legal and regulatory requirements.

To ensure robust data management, a dedicated data management suite has been developed, employing a security by design architecture. The suite is hosted on a secure Google business environment. It enables manual data entry into case report forms and facilitates bulk data upload via secure file transfer. This flexibility accommodates the diverse data infrastructures at the participating centres, where data is collected either in bulk from electronic health record-based databases or through manual review of medical charts. After initial data pre-processing and curation steps, the collected data are stored in a central relational database. This database includes several tables such as: patient information, hospitalisation data, SARS-CoV-2 virological data, study outcome, COVID-19 pharmacological treatment data, vital signs, clinical chemistry data, admission co-infection information, diagnoses/comorbidities, symptoms, biological samples and shipment information. In addition to clinical data, biological materials such as serum/plasma, peripheral blood mononuclear cells, nasopharyngeal blood viral isolates, and/or viral sequences are collected from selected patients for further analysis in WP2.

Whole blood samples are drawn and stored centrifugated and separated into plasma and/or serum. Whole blood is drawn in 2 × 4.5 mL tubes for analysis. In a subset of patients, peripheral blood mononuclear cells (PBMCs) are separated by Ficoll-Isopaque for assessment of cellular immunity against SARS-CoV-2. Serum and/or plasma are used for neutralisation assays and for assessment of SARS-CoV-2 diagnostics. The collection of biological samples is not mandatory and is performed only on a subset of patients.

In summary, the biological materials – where taken—includes:Plasma or serum samples for titration of neutralising antibodies.PBMCs for assessment of any pre-existing or vaccine-induced cellular-mediated immunity response to the different variants.Virus isolates from clinical specimens to enrich the repository of SARS-CoV-2 variants. Isolation procedures will be run as available at individual laboratories.When available, SARS-CoV-2 variant information is collected. In addition, full-length viral genomic RNA sequencing is run by the next-generation sequencing (NGS) platform available at the individual laboratories for selected patients.

Specific regulations exist regarding the international shipment of biological samples derived from study subjects. It is the responsibility of the investigator (assisted by the courier service and the coordinating centre) to ensure that all study samples for international transport are appropriately handled, packed, and shipped.

Plasma samples are stored in a repository/biobank at the site or shipped to the designated laboratory of the consortium, at -80° Celsius, and will be destroyed no later than December 31, 2045. All samples stored will be analysed and destroyed in accordance with current legal and ethical requirements.

Pseudo-anonymised patient data as well as viral variant data are collected in a secure centralised server at EuResist Network where all the cleaning and refactoring procedures will be run. Cleansed, harmonised data will then be stored in a relational database in the same centralised server. MariaDB RDBMS is being used both for the collection of data via the eCRF and for the storage of the cleansed data (Fig. 1).

